**OBJECTIVES:**

General:

We seek to establish the link between the presence, diagnosis and treatment of cervical dysplasia and HIV genital shedding. We also seek to establish the sensitivity and specificity of three resource-appropriate screening methods, VIA, VILI and p16^INK4a^ biomarker testing, for cervical dysplasia.

Specific (Aims):

**Aim 1:** **To calculate the sensitivity, specificity, and the positive and negative predictive values of visual inspection of the cervix after application of 3-5% acetic acid (VIA) and visual inspection with Lugol’s Iodine (VILI) for the diagnosis of cervical intraepithelial neoplasia grade 2 and grade 3 (CIN2/3) in HIV-infected women.** HIV-infected women enrolled in care at the FACES clinics in western Kenya will undergo VIA or VILI and colposcopy with directed biopsy as indicated. The colposcopy will be used as the reference standard, allowing for calculation of sensitivity, specificity, positive and negative predictive value of VIA and VILI.

Hypothesis 1: VIA and VILI will have test characteristics validating their use as a screening test for cervical dysplasia among HIV-infected women in resource-limited settings.

**Aim 2: To define the quantitative value of a biochemical assay for p16^INK4a^ that predicts cervical neoplasia with the greatest sensitivity and specificity among HIV-infected women using a receiving operating characteristic (ROC) curve.**

**Aim 2a: To compare the sensitivity and specificity of the p16^INK4a^ biochemical assay with that of HR-HPV testing.** HIV-infected women enrolled in care at the FACES clinics in western Kenya will undergo specimen testing for p16^INK4a^ and HR-HPV, followed by colposcopy with directed biopsy as indicated.

**Aim 2b: To calculate the sensitivity and specificity of the p16^INK4a^ biochemical assay for the detection of CIN2/3 using colposcopy as the gold standard.** HIV-infected women will have p16^INK4a^ specimens collected prior to colposcopy. Diagnosis for positive p16 will be based on the ROC curve cut-off determined in the pilot study, with colposcopy as the reference standard as above.

**Aim 2c: To investigate whether presence of increased baseline and follow-up levels of p16^INK4a^ in women with normal colposcopy or CIN1 is associated with increased risk of detecting CIN2/3 during one-year follow-up.** HIV-infected women enrolled in care at the FACES clinics in western Kenya who have had baseline p16^INK4a^ measurement, with normal colposcopy or CIN1 will be followed-up after one-year for repeat testing for p16^INK4a^, HR-HPV and colposcopy to compare rate of CIN2/3 between the two groups.

Hypothesis 2: The ROC curves for the biochemical assay for p16^INK4a^ will define a cut-off level for a positive result that will provide a sensitivity and specificity for CIN2/3 greater than those for HR-HPV testing in this population.

Hypothesis 2c: The risk of detecting CIN2/3 at one-year in women with normal colposcopy or CIN1 is increased in women with increased levels of p16^INK4a^ in cervical specimens at baseline and/or follow-up compared to women with normal or undetectable levels of p16^INK4a^.

**Aim 3: To measure and compare the quantity of HIV-1 RNA in the cervicovaginal secretions of women with cervical dysplasia to those with normal cervical exams.** We will measure and compare the presence and levels of cervicovaginal HIV-1 in women with biopsy-confirmed high-grade cervical dysplasia to those of women with no evidence of cervical disease. Cervical dysplasia will be defined as cervical intraepithelial neoplasia 2 or 3, or CIN2/3.

**Aim 3a: To determine the amount and duration of increased HIV-1 RNA shedding in the genital tract following cervical biopsy for suspected dysplasia.** We will measure the presence and levels of cervicovaginal HIV-1 in women prior to undergoing cervical biopsy and compare values to specimens taken on days 0, 2 and 7 following biopsy.

Hypothesis 3: Women with biopsy-confirmed CIN2/3 have higher odds of detectable genital HIV-1 viral load. Women undergoing biopsy will have an increase in genital HIV-1 RNA shedding that will return to baseline within 7 days post-procedure.

**Aim 4: To measure and compare the amount of HIV-1 RNA found in the cervicovaginal secretions in women before and after undergoing treatment for CIN2/3 with LEEP.**  Collection of specimens for detection and quantification of cervicovaginal HIV-1 viral load will be done immediately prior to the LEEP, and on post-procedure weeks 1, 2, 4, 6, 10 and 14 to determine the level and duration of increased genital shedding associated with the procedure.

Hypothesis 4: There will be a significant increase in HIV-1 genital shedding post-treatment which will return to baseline before 14 weeks post-treatment.

**DESIGN AND METHODOLOGY**

Study Site: This study will take place in FACES-supported clinics in the Nyanza Province of Western Kenya.

Study Population: The main target population for the proposed research is HIV-infected women enrolled in care at FACES-supported clinics in Nyanza Province.

Subject recruitment and enrollment: Women receiving care at FACES clinics will be considered for recruitment into the study. FACES patients are introduced to cervical cancer screening as part of an HIV education session when they enroll in care. Information about cervical cancer and the opportunity for screening is reinforced as part of a general daily health talk given while patients are waiting to be seen for their routine HIV care, and then reinforced through individualized counseling during their clinical visit. Women willing to undergo cervical cancer screening will be screened consecutively for their study eligibility and asked about their willingness to participate in the study. Inclusion and exclusion criteria are listed below:

| **Inclusion Criteria** | **Rationale** |
| --- | --- |
| Enrolled in HIV care at FACES | Allows for follow-up and shared utilities of space and personnel with FACES program |
| ≥ 23 yrs old | Based on WHO recommendations for established cervical cancer screening programs in resource-limited countries |
| Able to verbalize understanding of study procedures and provide informed consent | Ensure participant understanding and avoid potential coercion |
| *Additional Criteria for Specific Aim 2c:* |  |
| Participated in p16^INK4a^ ELISA pilot study and had a colposcopic finding of CIN1 or normal-appearing cervix ? | These women already have a baseline p16^INK4a^ biomarker level measured, hence qualify for follow-up study  Women with CIN2/3 would have undergone surgical treatment for their lesion, thus reducing their risk of disease at 1 year |
| *Additional Criteria for Specific Aim 3:* |  |
| On ARVs for at least 6 months with adherence >90% | Reflects majority of FACES clients and reduces confounding effect of ARVs on HIV-1 genital shedding^82^ |
| *Additional Criteria for Specific Aim 3a:* |  |
| Will undergo biopsy for positive colposcopic findings at one of the FACES study clinics in Kisumu |  |
| Willing to remain abstinent from sexual activities for one week post-biopsy | Reduces potential semen contribution to genital HIV-1 viral load measurements. |
| *Additional Criteria for Specific Aim 4:* |  |
| Will undergo LEEP for CIN2/3 at one of the FACES study clinics in Kisumu | Allows baseline specimen collection and ensures the quality and standard of the LEEP |
| Willing to remain abstinent from sexual activities for four weeks post-LEEP and for three days prior to each follow-up study visit | Reduces risk of post-LEEP bleeding and infection. Reduces potential semen contribution to genital HIV-1 viral load measurements. |
| Exclusion Criteria | Rationale |
| Pregnant | May increase false positive rate of VIA^75^ |
| Clinical evidence of cervical or pelvic infection:   - Muco-purulent discharge - Cervical friability - Cervical motion tenderness found on pelvic exam in symptomatic women | May increase false positive rate of VIA^75^ |
| Cervical cancer screening at FACES within past 12 months | May influence clinician interpretation of results |
| Prior or current history of cervical surgery, dysplasia or cervical cancer | May influence test characteristics of colposcopy and VIA |
| Unsatisfactory VIA | Woman would require alternative screening method (cytology, colposcopy or endocervical sampling) per WHO protocol^74^ |
| *Additional Criteria for Specific Aims 3 & 4:* |  |
| Laboratory evidence of cervical infection:   - NAAT for Gonorrhea or Chlamydia - Wet mount showing bacterial vaginosis, candida or trichomonas | Concomitant sexually transmitted infections can increase the risk of HIV-1 genital shedding |

We will sequentially recruit and enroll eligible women for all specific aims. There will be three separate consent forms (Appendix A, B and L). Screening and informed consent for participation in the studies involving VIA or VILI, colposcopy and specimen collection (S.A. 1, 2 and 3) will take place in a private gynecologic exam room prior to pelvic exam. Because satisfactory visual exam or clinical evidence of cervical or pelvic infection will only become evident after exam, participant numbers will be assigned after VIA and colposcopy. Women who are unsure about enrollment and would like time to consider will be given an information sheet (Appendix C) and may return for enrollment at a later date. VIA in these women will be deferred until their next visit. Eligibility and informed consent for the post-LEEP genital shedding sub-study will take place at a clinical visit, prior to their LEEP procedure. Women will be given an information sheet specific to this part of the study, in addition to the normal clinical materials in use that explain the LEEP procedure (Appendix D).

Statistical Considerations and Sample Size Calculation

**Specific Aim 1:** To calculate a sensitivity of 75% with a confidence interval of 5% in both directions and a two-sided alpha of .05, we will need to complete sequential VIA and colposcopy in ***1800* women**.^83^

To determine a specificity of 80%, with a confidence interval of 5% in both directions and a two-sided alpha of .05, we calculate that we will need to examine 400 women. Because the scientific outcome of specificity is most important, we will use the estimate of 1,800 women (900 VIA and 900 VILI to account for laboratory and sampling error) to power our study.

**Specific Aim 2:** We based our sample size calculations for this aim on the following calculations: a sample of 42 women with positive results and 60 with negative results will achieve 90% power to detect a difference of 0.1 between the histology result and the AUC for the p16^INK4a^ assay using a two-sided z-test at a significance level of 0.05.^84^ Histology is the gold standard for diagnosis of CIN, which would give it an AUC of 1.0; a 0.1 difference mean an AUC for p16^INK4a^ of 0.90, which would make it an excellent diagnostic tool. Our power to detect even greater difference with this sample size would be even greater. We will enroll ***60* women with negative colposcopies, and *140* women with positive colposcopic exams**. The positive predictive value of a positive colposcopy at FACES is approximately 57% for CIN2/3 and 89% of any diagnosis of CIN.^85^ A sample of 140 women with positive colposcopic exams will ensure that we have an adequate number of women with the positive result of interest (CIN2/3) to achieve our specific aim, and potentially enough women with lower levels of CIN to obtain preliminary information regarding test characteristic among this group. In order to calculate the specificity and sensitivity (SA 2b), we will use the sample sizes calculated above for specific aim 1.

Specific Aim 2c: To investigate whether increased levels of p16^INK4a^ in women with normal colposcopy or CIN1 puts them at higher risk for detecting CIN2/3 after one year, we use an effect size from literature to calculate our sample size. This question has not been previously studied in HIV+ women in resource-limited settings. A previous study of HIV-negative women in North America found that women with CIN1 with diffuse staining for p16^INK4a^ had between 26.9 – 33.6% increased risk of CIN2/3 detection during follow-up compared to those with weak or no staining for p16^INK4a^.^17^ Using this effect size, with a two sided alpha of .05 and power of 80 percent, we will need between **39 - 55 subjects with CIN1 diagnosis** in each group (with and without elevated p16^INK4a^) to show a similar or greater effect size (total 78-110 participants). Wang et al (2004) looked at both women with normal colposcopy and CIN1, and found that those with positive p16^INK4a^ staining at baseline had a 23.8% higher rate of progression to CIN2/3 during follow-up compared to those with negative staining.^16^ Using this effect size to estimate sample size, we need to study 82 subjects with normal colposcopy each in the biomarker positive and biomarker negative groups (total 164) to establish a similar effect size with 80% power. From the p16^INK4a^ pilot study, we have a total of 55 women found to have CIN1 and 190 women who had normal colposcopy, with about half of each group having increased levels of the biomarker. Based on this, we will be **a bit shy of the 39-55 participants** needed in the CIN1 group to show a similar effect size as the study quoted. However, we believe we can still be able to show a smaller yet clinically important effect size. For participants with normal colposcopy at baseline, we have sufficient number of women from the pilot study with this finding, such that with aggressive follow-up we should be able to show a similar or greater effect size as that seen in literature. Because this is an exploratory study, even if we are unable to achieve power for some of the sample sizes we are using, the results will be important for suggesting further research.

**Specific Aim 3:** Our sample size calculation is based on the frequency of cell-free HIV-1 RNA detected among women with CIN or HR-HPV in the two studies mentioned above. In the earlier study of HAART naïve women by Spinillo, et al, 81% of women with HR-HPV had measurable HIV-1 RNA in their cervicovaginal secretions compared to 55% of women without HR-HPV (OR 8.63).^86^ In a second study, by the same authors, 40% of women with CIN had measurable HIV-1 RNA in their cervicovaginal secretions, compared to 17% of women without CIN (OR 1.86).^68^ Extrapolating from the results of these studies, we anticipate a difference of HIV-1 detection frequency between cases and controls of approximately 25%; we would consider a difference of this magnitude to be clinically significant. To obtain a power of 80% with a two-sided alpha of 0.05 to detect this difference, we would need to enroll 46 women per study arm.^87^ In order to ensure that we have sufficient power, we will **enroll *50* women in both arms**. Aim 3a is an exploratory pilot study from which we hope to obtain descriptive data to inform future studies. Therefore we did not calculate a sample size. We will evaluate 30 women for this study, using guidance from the sample size calculation listed below.

**Specific Aim 4:** Sample size calculations for Aim 4 focus on estimation of the mean change in viral load between baseline and one week of follow-up. A sample size of 30 will provide sufficient power to address hypotheses of interest, and will also allow investigation of factors related to observed changes in viral load. We assume a standard deviation of 1.7 log copies for both the baseline and follow-up measure, that the correlation between the baseline and follow-up measure will be 0.7, and that change will be evaluated using a t-test for paired measurements. This calculation is based on variability estimates from Coombs et al., who examined genital tract shedding in 55 women using Sno-Strips, cytobrush and cervicovaginal lavage measures. They found Sno-Stripscalc to be the least variable measure, with a within-individual standard deviation of 0.55 log copies of viral RNA and a between-individual standard deviation of 1.66 log copies. Although preliminary data are not available to inform more detailed calculations, we anticipate similar levels of power to address hypotheses concerning post-treatment changes. With these assumptions, ***30* participants** should provide at least 80% power to detect within-individual changes (measured as the difference between pre and post-treatment levels) as small as 1 log as significant at the 5% level. Power to detect change as small as 1.5 logs will exceed 95%. These results indicate that we have sufficient power to detect clinically important changes, and will also be able to investigate patterns of change over the entire course of follow-up.

Study Design

We propose a ***cross-sectional*** study to evaluate this specific aim. Each participant will undergo a VIA or VILI with specimen collection for p16^INK4a^ and HR-HPV and colposcopy by a different clinician during a single clinic visit. The study clinician performing the colposcopy will be blinded to the results of the VIA or VILI. For women in the VILI arm, the colposcopy will be performed first in order to eliminate any interference with colposcopy interpretation from the iodine staining. Biopsy decisions will be made at the time of colposcopy, but deferred until after the VILI. Any woman with cervical lesions suspicious for dysplasia seen at the time of colposcopy will undergo biopsy. Colposcopy will be used as the reference standard for presence or absence of CIN2/3, with biopsy results being the final diagnosis when available. Women with a normal colposcopy without biopsy will be considered to have no disease.Specific Aims 1, 2, 2a and 2b)

We propose a **prospective cohort** study using a subset of women identified from the cross-sectional study in Specific Aims 1 and 2a to evaluate specific aim 2c during a one-year follow-up visit. We will recruit women for this follow-up study who participated in the pilot p16^INK4a^ ELISA study (Aim 2a) and had normal colposcopy or CIN1. In a single visit, each participant will undergo a VIA with specimen collection for p16^INK4a^ and HR-HPV followed by colposcopy and biopsy if needed.

We propose a ***case-control*** study to measure and compare the presence and quantity of HIV-1 RNA in the cervicovaginal specimens of women with biopsy-confirmed CIN2/3 (cases) and age-matched women without evidence of cervical disease as measured by negative VIA (controls). We will compute the odds ratio for HIV-1 detection and compare log transformed mean viral loads between cases and controls. (Specific Aim 3)

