**Single Follow-up visit**: Informed consent, VIA, colposcopy, and cervical specimen collection for HR-HPV, and p16^INK4a^ will take place during a single follow-up visit for women who previously underwent p16^INK4a^ testing and meet criteria for these specific aims. If indicated by abnormal findings at colposcopy, participants will undergo directed biopsy at the time of colposcopy for diagnosis of cervical dysplasia. No biopsies will be performed solely for study purposes.

Specific Aim 4 (7 study visits):

**Enrollment:** Women returning for their biopsy results who have CIN2/3 will be offered treatment with LEEP at this visit, as is the current clinic protocol at FACES. Recruitment and enrollment into the post-LEEP HIV-1 shedding study will take place at this visit. Women who meet eligibility criteria will be offered enrollment. Informed consent for this study will be obtained during this visit, and participants will be assigned a study ID number. A follow-up visit schedule will be made.

**Follow-up Visits at 1, 2, 4, 6, 8, 10 and 14 weeks:** Participants will undergo a brief interview followed by a sterile speculum exam with specimen collection for genital HIV-1 RNA.

Study measurements

Individual participant data, including demographic and clinical information will be collected from the paper medical record using study-specific data collection forms. Individual and de-identified aggregate data will be abstracted from the electronic medical record system (OpenMRS) in place at FACES. Participants will all be enrolled in FACES for care of their HIV disease; as part of this care, they have regular laboratory monitoring of CD4+ counts, hemoglobin levels and basic serum chemistries. Laboratory data for the study, apart from histology and HIV-1 RNA specimens, will be obtained from their FACES charts, and will not be collected independently for the study.

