**ETHICAL CONSIDERATIONS**

Human Subjects Involvement and Characteristics

The study described in this proposal will involve a total of around 1,800 HIV-infected women receiving care at the FACES clinics in Kisumu, Kenya. Women will be included in the study for the cross-sectional validation study if they are: 1) 25 years or older 2) not pregnant 3) accept cervical cancer screening 4) have a satisfactory Visual Inspection with Acetic Acid (VIA). Participants will be recruited for the prospective follow-up study (Specific Aim 2c) if they meet the above criteria, and were found to have normal colposcopy or CIN1 upon initial screening with p16^INK4a^ biomarker measurement. Participants will be recruited for the prospective post-LEEP HIV-1 shedding study if they meet the above criteria, have undergone LEEP for treatment of CIN2/3 and agree to remain abstinent for three days prior to each of the follow-up visits. To participate in any of these study activities, women must be willing and able to participate, be able to sign or mark a consent form, and speak one of the languages into which the consent form and data collection instruments have been translated, including English, D’Luo and Kiswahili.

Sources of Materials

Data for this study will be collected from several sources. Clinical and demographic data will be obtained through chart reviews and physical examination. We will also obtain clinical information from the colposcopic examinations. Information from the colposcopy and if performed, biopsy, will be entered into the participants’ medical records as it will be used to direct clinical care. We will also obtain cervical specimens for p16^INK4a^ and HR-HPV testing and vaginal wick specimens for women in the post-LEEP HIV-1 shedding study. These will be obtained solely for research purposes, and will therefore not be entered into the participant’s medical record. All data collection will take place in a private study room.

Potential Risks

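### Abstinence is required only for the post-procedure samples in Aims 3a and 4, so later change from baseline may be confounded with change in semen exposure, in a direction the protocol does not settle

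*Protocol*

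**What the plan says.** The inclusion criteria table (Design and Methodology) sets the Aim 3a condition as "Willing to remain abstinent from sexual activities for one week post-biopsy", with the rationale "Reduces potential semen contribution to genital HIV-1 viral load measurements". The Aim 4 condition is "Willing to remain abstinent from sexual activities for four weeks post-LEEP and for three days prior to each follow-up study visit". Its rationale names post-LEEP bleeding and infection first, then semen contribution. Ethical Considerations restates the Aim 4 condition for follow-up only: women must "agree to remain abstinent for three days prior to each of the follow-up visits".

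Under Objectives, Aim 4, specimen collection "will be done immediately prior to the LEEP, and on post-procedure weeks 1, 2, 4, 6, 10 and 14". Under Study visits, Specific Aim 4, "Women returning for their biopsy results who have CIN2/3 will be offered treatment with LEEP at this visit", and recruitment and consent for the post-LEEP study take place at that same visit. For Aim 3a, Study Design places sampling before biopsy, immediately after it, and on days 2 and 7. Study Design and the Aim 4 analysis text both express results as change from the pre-procedure value.

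**The concern.** The protocol treats semen as a possible contaminant of its own outcome and controls for it on one side of a within-woman contrast only. The baseline sample carries no abstinence condition, and the text does not say that recent intercourse is recorded there. A difference between baseline and a later sample can then reflect the procedure, a change in semen exposure, or both. Recruiting more women does not separate them. A mixed model does not either, because one unconditioned baseline anchors all the follow-up weeks.

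Hypotheses 3 and 4 concern a rise and its return to baseline. A baseline raised by semen-derived RNA would shrink the apparent rise and bring forward the apparent return. The Justification says the results could affect the recommended length of post-procedure abstinence, and Expected Application of Results says they will guide counselling. An error in that direction would be falsely reassuring.

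**Working it through.** **1. Where the asymmetry applies**

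| Contrast | Condition on reference sample | Condition on comparison sample | Asymmetric? |
| --- | --- | --- | --- |
| Aim 3a, immediately after biopsy vs before | none | none (same visit) | no |
| Aim 3a, days 2 and 7 vs before | none | abstinence after biopsy | yes |
| Aim 4, each follow-up week vs pre-LEEP | none | four weeks, and three days before each visit | yes |
| Aim 3, cases vs controls | none | none (both sampled at the single study visit) | no |

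Nothing else in the text closes the gap. The Aim 3a week of abstinence ends before the results visit at two to four weeks, so women in both sub-studies are not covered at the LEEP baseline. The Predictor Variables and the confounders in the analysis section include marital status and number of partners, but not recent intercourse.

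**2. The plan's own precision (Sample Size, Specific Aim 4)**

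Inputs: n = 30, SD 1.7 log at each time, correlation 0.7, paired t-test, 5% level (taken as two-sided).

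- SD of change = 1.7 × √(2 × (1 − 0.7)) = 1.317 log.
- Standard error of the mean change = 1.317 / √30 = 0.240 log.
- Power by noncentral t: 98.0% for 1 log and above 99.9% for 1.5 logs. The stated bounds (at least 80%, above 95%) hold. The power statement is not at fault.

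**3. What unequal exposure would do (assumed inputs)**

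Let f₀ and f₁ be the shares of women with semen in the baseline and follow-up samples, and k the resulting change in log copies. Then observed mean change = true change − (f₀ − f₁) × k. If abstinence is kept at follow-up, f₁ = 0 and the shift is −f₀ × k. The documents give neither f₀ nor k. For a true rise of 1 log, with the extra variance f₀(1 − f₀)k² included:

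| f₀ | k | Shift (log) | Shift / 0.240 | Observed rise | Power |
| --- | --- | --- | --- | --- | --- |
| 10% | 0.25 | −0.025 | 0.1 | 0.975 | 97.5% |
| 25% | 0.5 | −0.125 | 0.5 | 0.875 | 93.4% |
| 25% | 1.0 | −0.25 | 1.0 | 0.75 | 81.7% |
| 50% | 0.5 | −0.25 | 1.0 | 0.75 | 84.2% |
| 50% | 1.0 | −0.50 | 2.1 | 0.50 | 46.8% |

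Positive k requires an HIV-infected partner. Since the Background says most infected people have HIV-negative partners, the 50% rows are best read as an outer limit.

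If semen adds volume but no RNA, k is zero or negative. The outcome is defined, under Aim 3, per microliter of vaginal fluid, so dilution is possible. With f₀ = 25% and k = −0.25, the shift is +0.0625 log and the rise is overstated.

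**4. The duration claim**

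The shift matters most where the true residual is small. With f₀ = 25% and k = 1.0, a true residual rise of 0.25 log would appear as 0.25 − 0.25 = 0, that is, as a return to baseline.

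**The case against.** Direction is the strongest objection. A reader might infer that semen can only raise the baseline, so that the post-procedure rise is necessarily understated. The documents do not support this. The Background says most partners are HIV-negative; their semen adds no HIV-1 RNA and may dilute the sample. A downward bias would also work against the first half of Hypotheses 3 and 4, which predict an increase, and would help only the return-to-baseline half.

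A reader might also take every follow-up value as free of semen, or extend the point to Aim 3. Neither holds. The criteria ask for willingness to abstain, the same-visit post-biopsy sample shares its baseline's exposure, and Aim 3 cases and controls are sampled under one rule. Nor should a worst-case size be taken as the estimate: 30% exposed with a 1.5 log increase gives 0.45 log, or 0.45 / 0.240 = 1.9 standard errors, but this joins the upper ends of two assumed ranges. Their lower ends, 10% and 0.5 log, give 0.05 log, or 0.2 standard errors.

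Three further points have weight. The bleeding-and-infection rationale explains why the four-week period is post-procedure only, which leaves the three-day condition as the one about semen. The data collection and interview forms are listed but not reproduced, so they may already ask about intercourse. Aim 3a is an exploratory pilot, and Aims 3 and 4 are described as preliminary.

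These objections narrow the point without removing it. The baseline condition is absent from all three places where abstinence is stated, and exposure not recorded at baseline cannot be adjusted for later.

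**Conclusion.** The point holds as a potential confounding of uncertain direction. The pre-biopsy and pre-LEEP baselines are potentially semen-exposed, while the days 2 and 7 samples (Aim 3a) and all follow-up weeks (Aim 4) fall under an abstinence condition. The rise and its duration would be understated where the partner is HIV-infected. With an HIV-negative partner there may be no bias, or the opposite one. Neither direction nor size is established by the documents. Under the assumptions tabulated, the shift runs from about 0.025 to 0.5 log downward, and it changes sign under dilution. In most of those scenarios a 1-log rise would still be detected with more than 80% power. The more exposed conclusion is the time of return to baseline. This is a cheap improvement worth making, and it does not show that the sub-studies will give a wrong answer.

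**What to change.** 1. Reconcile the baseline and follow-up sampling conditions in the Aim 3a and Aim 4 inclusion criteria and in Ethical Considerations, so that the protocol says what applies to the reference sample.
2. Record the date of last vaginal intercourse and condom use at every HIV-1 RNA sample, including the pre-biopsy and pre-LEEP baselines. If the unreproduced forms already ask this, state it in the protocol.
3. Prespecify a change-from-baseline analysis that adjusts for recent unprotected intercourse, or a sensitivity analysis that excludes baselines taken within three days of it. Either can be used whichever way the bias runs.
4. Where the LEEP sample is taken at a visit after consent, the existing three-day sampling condition can also be applied to that baseline. It cannot readily be applied where consent and sampling share a visit, as with the Aim 3a baseline and same-visit LEEP. There, recording and flagging is the workable part.

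The cost is two interview questions per sampling visit and a few women lost from the sensitivity contrast. Clinical care is unchanged.
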